## Background

In 2021, almost half of patients in German hospitals were 65 years and older [1]. Older age is associated with cognitive impairment, with a prevalence among elderly hospital patients ranging from 40 to 67.5% [2, 3]. This mainly includes people living with dementia, mild cognitive impairment, and with delirium [3].

Hospitalisation of people with cognitive impairment is associated with several challenges. One challenge is a frequently missing formal diagnosis of cognitive impairment [2, 3], resulting in care that is not tailored to the needs of this vulnerable patient group. An integrative review on hospital outcomes [4] found, that people with cognitive impairment encounter a hospital environment focussed on acute illness rather than their individual needs, as shown by avoidable bed moves, inadequate pain management, inappropriate catheterisation, and poor communication and relationship building with healthcare professionals. Negative experiences are common, frequently leading to feelings of fear and an increase in behavioural and psychological symptoms. In addition, people with cognitive impairment are more likely to encounter a range of related adverse events such as the incidence of delirium, urinary tract infections, pneumonia, pressure ulcers, adverse drug reactions, and falls, that may lead to prolonged hospital stays and increased mortality [4]. Healthcare professionals struggle with the discrepancy between desirable hospital care and the current reality of care for people with cognitive impairment, resulting in distress and frustration, uncertainty in dealing with changed behaviour, conflicting priorities, and the inability to meet individual needs [5].

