The development and implementation of an EPN role is complex as various components and their interactions need to be taken into account. To comprehensively investigate complex interventions, the guidance of the British Medical Research Council (MRC) recommends the evaluation of effects, while considering underlying processes and influencing factors as well as costs [26].

In the ENROLE-acute (Expanded Nursing ROLEs for person-centred care for people with cognitive impairment in ACUTE care) project, we are developing, implementing, and evaluating a complex PCC intervention for people with cognitive impairment, delivered by EPN on peripheral wards in one acute hospital. We hypothesise that by introducing PCC, the individual needs of people with cognitive impairment will be addressed in a timely manner and thus adverse events will be reduced or avoided, leading to a reduction in the length of hospital stay.

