##### Patient level

We defined the following inclusion criteria for potential participants: (1) age of 65 years and older, (2) sufficient knowledge of German language, (3) hospital stay of unclear duration or over 48 h, (4) ability to consent or existence of a legal representative, and (5) present cognitive impairment (e.g., diagnosis of dementia) or risk for cognitive impairment (e.g., risk for delirium) according to predefined criteria.

We will recruit potential participants on six days a week over a time period of six months. Contact persons of the respective wards will inform eligible people with cognitive impairment and, if necessary, their representatives about the study and ask for consent to be approached by the research team for obtaining informed consent.

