**PEOPLE WITH COGNITIVE IMPAIRMENT**					
Length of hospital stay	Single item	Number of days people with cognitive impairment stayed in hospital during a single admission event [34]	Patient records	t_5_	Primary outcome
Prevalence of delirium	Confusion Assessment Method – short form (CAM)	The Confusion Assessment Method consists of 4 items on (1) acute onset and/or fluctuating course, (2) inattention, (3) disorganised thinking, and (4) altered level of consciousness. Delirium is indicated sensitively if item (1) and (2), and either (3) or (4) are scored positive [35–37]	Rating by research team	t_1_, t_2_, t_3_, t_4_, t_5_	Secondary outcome
Severity of delirium	Confusion Assessment Method – Severity (CAM-S)	Delirium severity is measured using the Confusion Assessment Method by rating the items in terms of severity (0 = absent, 1 = mild, 2 = marked). The item (1) acute onset and/or fluctuating course is only rated as 0 = absent or 1 = present. Overall, the scale ranges from 0—7 points, with higher values indicating a more severe degree [38]	Rating by research team	t_1_, t_2_, t_3_, t_4_, t_5_	Secondary outcome
Delirium subtype	Delirium Motor Subtype Scale (DMSS)	The Delirium Motor Subtype Scale consists of two subscales on hyperactive (4 items) and hypoactive (7 items) subtype, classifying four different motor subtypes: hypoactive, hyperactive, mixed or no motor subtype. Each item is scored dichotomously (present or absent) over the past 24 h. Hyperactive delirium is positive, when two items on the hyperactive subscale are present. Hypoactive delirium is positive, when either “decreased amount of activity” or “decreased speed of actions” in combination with at least one other item is present. Mixed type is positive, when both hyper- and hypoactive delirium was positive within the last 24 h [39, 40]	Rating by registered nurses	t_1_, t_2_, t_3_, t_4_, t_5_	Secondary outcome
Prevalence of pain	Numeric Rating Scale (NRS)	The Numeric Rating Scale is a 11-point scale ranging from 0 (no pain) to 10 (worst possible pain) [41]. A value ≥ 1 indicates pain	Self-rating by people with cognitive impairment	t_1_, t_2_, t_3_, t_4_, t_5_	Secondary outcome

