#### Assignment of intervention

Allocation of wards as intervention or control ward was based on ward managers’ decision to participate in the intervention. Participants’ assignment will be determined by their wards’ assignment.

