#### Data analysis

Statistical analysis is according to intention-to-treat (no exclusions). We will evaluate the primary outcome length of hospital stay by the stratified log-rank test (death is censored). Nota bene, the stratified log-rank test has very similar characteristics as the stratified van-Elteren rank-sum test and is available in many (statistical) software packages. We will use a propensity score approach (PSA) to balance individual characteristics between participants in intervention and control groups. In the multivariable logistic regression for PSA, we will use the independent variables age, gender, severity of cognitive impairment, Charlson Comorbidity Index, admission type, expected admission diagnosis-related or ward-related length of stay, and hospitalisations during the last 7 days [66, 67] as these variables are likely to be associated with outcome. Moreover, we will carefully monitor mortality in both arms, although we do not expect any difference. We will evaluate secondary outcome measures by (generalised) mixed models for repeated measures over time. If feasible, we will take outcome measures (particularly those reported by people with cognitive impairment) over the course of hospital stay. Thus, we may need to evaluate the outcome trajectories by random coefficient models. We will categorise and compare safety outcomes by frequency, relatedness, seriousness, and severity. Moreover, we will summarise variables by mean, standard deviation, and percentiles (0, 25, 50, 75, and 100) respectively by absolute and relative frequencies (percentage). Due to the small number of clusters, we will at least account for them in a fixed effect analysis. Though we will attempt to estimate corresponding random effects (e.g., to derive intraclass correlation), this seems prone to bias.

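### The admission delirium rating is listed as an outcome and not used for adjustment, so a difference between arms on arrival can bias the delirium comparison

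*Protocol article*

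**What the plan says.** - **Outcome.** Table 1 has a row "Prevalence of delirium", rated with the CAM at t1 to t5, and a row for severity, rated with the CAM-S at the same times. Both rows are typed as secondary outcomes in full. The table's footnote defines t1 as admission.
- **Model.** The Data analysis section under Evaluation of effects says: "We will evaluate secondary outcome measures by (generalised) mixed models for repeated measures over time". It adds that trajectories may need random coefficient models. It gives the t1 rating no separate role.
- **Adjustment.** The propensity score uses age, gender, cognitive severity, comorbidity, type of admission, expected stay and recent hospitalisations. Delirium at admission is not on that list, nor among the control variables in Table 1, where cognition is measured by the MoCA.
- **Population.** Eligibility covers "present cognitive impairment (e.g., diagnosis of dementia) or risk for cognitive impairment (e.g., risk for delirium) according to predefined criteria". The Background says of cognitive impairment in older inpatients: "This mainly includes people living with dementia, mild cognitive impairment, and with delirium". Nothing in the text shown excludes delirium present on arrival; the detailed criteria are in Additional file 2, which is not shown.
- **Allocation.** "Allocation of wards as intervention or control ward was based on ward" managers' decision to take part in the intervention.
- **Rationale.** The Background lists "adverse events such as the incidence of delirium" among the problems of hospitalisation. It hypothesises that needs will be met in time and "thus adverse events will be reduced or avoided, leading to a reduction in the length of hospital stay".

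**The concern.** The t1 rating describes the patient before the ward's care can have had much effect. In a non-randomised comparison of three wards against three, it is the most direct measure of whether the arms began with the same amount of delirium. The plan collects it but files it with the outcomes and leaves it out of both adjustment lists. If one arm admits more people who are already delirious, part of that difference persists in the later ratings and can be mistaken for an effect or hide one.

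There is also a question of interpretation. A participant delirious on arrival and one who becomes delirious on the ward count alike in prevalence at a given occasion. Fewer positive ratings may mean that delirium was prevented or that it resolved sooner. The later, larger trials that this study is meant to inform would need to know which. Table 1 does draw this line elsewhere: it counts only antipsychotics started during the stay.

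**Working it through.** **The plan's own figures.** The article gives no rate, effect or power for delirium. Its one power figure concerns length of stay and reproduces:
- pooled SD = √((18² + 16²)/2) = 17.03 days
- design effect = 1 + 119 × 0.05 = 6.95
- effective n per arm = 360/6.95 = 51.8
- 3/(17.03 × √(2/51.8)) = 0.897, so power at one-sided 50% is Φ(0.897) = 81.5%

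This has no bearing on the delirium outcome.

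**Assumptions for delirium (none is in the document).**
- p0 = share delirious at t1, 10% to 30%
- i = share positive at a later visit among those negative at t1: 20% control, 14% intervention (risk ratio 0.70, difference 6.0 points)
- q = share still positive at that visit among those positive at t1: 50%, the same in both arms

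Prevalence at a later visit = p0 × q + (1 − p0) × i.

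**1. Prevention and resolution mixed.** With equal p0 and q in both arms, the first term cancels and the difference is (1 − p0) × 6.0 points.

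| p0 | Control | Intervention | Difference (points) | Ratio |
|---|---|---|---|---|
| 10% | 0.05 + 0.90 × 0.20 = 23.0% | 0.05 + 0.90 × 0.14 = 17.6% | 5.4 | 0.765 |
| 20% | 0.10 + 0.80 × 0.20 = 26.0% | 0.10 + 0.80 × 0.14 = 21.2% | 4.8 | 0.815 |
| 30% | 0.15 + 0.70 × 0.20 = 29.0% | 0.15 + 0.70 × 0.14 = 24.8% | 4.2 | 0.855 |

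The difference does not depend on q; the ratio does.

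**2. Imbalance at arrival with no true effect.** Set i = 20% in both arms, with t1 delirium 20% in control and 15% in intervention.
- Control: 0.20 × 0.5 + 0.80 × 0.20 = 26.0%
- Intervention: 0.15 × 0.5 + 0.85 × 0.20 = 24.5%
- Spurious difference: 1.5 points, which is (q − i) × 5 points. It is 0.5 points for q = 30% and 3.0 points for q = 80%.
- If a model weighted t1 to t5 equally with t1 as a response: 0.2 × 5 + 0.8 × 1.5 = 2.2 points.

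**3. Does a contrast of change from t1 remove it?** Not in this example.
- Control rises by 26.0 − 20.0 = 6.0 points and intervention by 24.5 − 15.0 = 9.5 points, a spurious harm of 3.5 points.
- On the odds scale, control is (0.26/0.74)/(0.20/0.80) = 1.405 and intervention is (0.245/0.755)/(0.15/0.85) = 1.839. Their ratio is 1.31.
- The sign of the bias has flipped, because some delirium present on arrival resolves.

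**4. Does conditioning on t1 remove it?** Yes, in this example. Among t1-negative participants the later prevalence is 20% in both arms, and among t1-positive participants it is 50% in both.

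**The case against.** Four objections carry weight.

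- **The model is not fully stated.** Table 1 lists data-collection times, and the Data analysis section names only a class of models. Whether t1 enters as a response, an intercept or a covariate is ordinary content for an analysis plan, which is not shown. This stands against any claim that the plan has fixed a biased model. It does not explain why admission delirium is missing from the explicit propensity list and from the control variables. Step 3 shows that a group-by-time contrast is not a full substitute for conditioning.
- **Prevalence is a legitimate measure.** The hypothesis speaks of events being reduced as well as avoided, and the wording on incidence comes from the background summary of a review. This stands. Prevalence by occasion should be kept.
- **Other variables may help.** Cognitive severity and type of admission may carry part of an arrival imbalance, and the Discussion openly concedes a high risk of selection bias. Neither replaces a direct rating of delirium.
- **The share delirious at t1 is unknown.** Additional file 2, or the requirement for ability to consent or a legal representative, may keep it low. This limits the size of the problem, not its direction.

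A reader might infer something stronger: that most of a preventive effect is lost, with a true ratio of 0.70 becoming 0.81 to 0.91 and a 5-point imbalance becoming a 4-point difference. Those figures belong to an endpoint of ever being CAM-positive from t1 onward, which the plan does not contain. Nor do the documents support the reading that the trial cannot separate prevention from resolution: the planned individual ratings would allow it.

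**Conclusion.** The point holds in a limited form. Delirium at admission is measured but is given no baseline role in a comparison where wards chose their arm, and this leaves an avoidable route for bias. Under the stated assumptions, a 5-point imbalance at arrival produces about 1.5 points of spurious difference at a later visit (0.5 to 3.0 points for persistence of 30% to 80%). A preventive difference of 6.0 points appears as 5.4 to 4.2 points for 10% to 30% admission delirium. That shrinkage is not an error in estimating prevalence; it shows that prevalence answers a broader question than prevention. All delirium rates here are assumed, and equal persistence in both arms is assumed throughout. The matter concerns secondary outcomes of an exploratory trial and does not invalidate the primary analysis of length of stay. It is still worth correcting, because the remedy uses data already planned.

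**What to change.** 1. State that the t1 CAM and CAM-S are baseline covariates in the delirium models, and that t2 to t5 are the outcome occasions.
2. Add delirium at admission to the propensity model.
3. Keep prevalence by occasion as the planned outcome.
4. Add two supplementary analyses: new delirium at fixed occasions (for example day 3 and day 7) among participants CAM-negative at t1, and persistence and CAM-S severity among those CAM-positive at t1.

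**Cost.** The change is to analysis wording only, since the t1 ratings are already collected. If one propensity score also serves the primary outcome, step 2 alters that analysis too, so it should be settled before the data are examined. The supplementary subsets are smaller. Detection of new delirium depends on how long a participant stays, and length of stay is the primary outcome: an arm with shorter stays has fewer ratings in which to find delirium. The new-delirium results must therefore not be collapsed into a count of participants ever positive without accounting for length of stay.

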Person-centred care	Individualised Care Scale (ICS)	The Individualised Care Scale consists of 17 items measuring the perspective of people with cognitive impairment on implementation of individualised care during hospitalisation. Items are rated with a 5-point Likert scale ranging from 1 = strongly disagree to 5 = strongly agree. A general score is calculated as mean value between 1 and 5, with higher values indicating more individualised care [55, 56]	Self-rating by people with cognitive impairment	t_5_	Secondary outcome
Falls	Single items	Number of falls documented	Patient records	t_5_	Secondary outcome (safety outcome)
Physical restraints	Single items	Occurrence of the use of physical restraints	Retrospective rating by registered nurses	t_2_, t_3_, t_4_, t_5_	Secondary outcome (safety outcome)
Prescription of antipsychotics	Predefined list	Newly prescribed antipsychotic medication during hospitalisation	Patient records	t_5_	Secondary outcome (safety outcome)
Mortality	Single items	People with cognitive impairment that died during data collection	Patient records	t_6_	Secondary outcome (safety outcome)
Stability of care arrangements	Single items	• Number of readmissions within 30 days • Perceived stability of care arrangement	Telephone interview with people with cognitive impairment and/or their relatives	t_6_	Secondary outcome (safety outcome)
Sociodemographic variables	Single items	• Age in years • Gender: Male, female, or divers • Care dependency levels ranging from 1 to 5 • Care situation before admission	Patient records	t_1_	Control variable
Admission diagnosis	Single items	Admission diagnosis as documented	Patient records	t_5_	Control variable
Type of admission	Single items	Emergency or planned admission	Patient records	t_1_	Control variable
Previous hospital admissions	Single items	Number of hospital admissions within the last seven days	People with cognitive impairment and/or their relatives	t_1_	Control variable
Admission diagnosis-related (diagnosis related groups) length of hospital stay	Single items	Mean stated length of stay of the patient's diagnosis-related group	Patient records	t_5_	Control variable
Or Ward-related length of hospital stay		Minimum length of stay of special wards, e.g., based on rehabilitation programmes	Ward managers	t_0_	
Type of discharge	Single items	Discharge home, transfer	Patient records	t_5_	Control variable

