**STAFF**					
Distress associated with difficult behaviour for people with cognitive impairment	Residents’ Challenging Behaviour related Distress Index	The Residents’ Challenging Behaviour related Distress Index includes 10 items that address altered behaviour such as hallucinations, instability, anxiety, depression, apathy, euphoria, limited communication skills, disinhibition, aggression, and impaired motor skills. All items are rated in terms of the degree of distress 1 = does not stress me at all, 2 = stresses me somewhat, and 3 = stresses me a lot. The score ranges from 0—100 points, with a higher score indicating higher distress [60]	Self-rating by staff	t_0_, t_7_	Secondary outcome
Person-centred care	Person-Centred Practice Inventory – Staff (PCPI-S)	The Person-Centred Practice Inventory—Staff includes 59 items covering 17 different constructs of person-centredness with respect to 3 domains: prerequisites, care environment, and person-centred processes. The items are measured on a 5-point Likert scale from 0 = strongly disagree to 4 = strongly agree. Overall, the scale shows a sum score of 0—100, with higher scores representing greater agreement with person-centredness [61, 62]	Self-rating by staff	t_0_, t_7_	Secondary outcome
Sociodemografic variables	Single items	• Age in years • Gender	Self-rating by staff	t_0_, t_7_	Secondary outcome

^a^t_0_ = before implementation of intervention; t_1_ = admission; t_2_ = day 3 of hospital stay; t_3_ = day 7 of hospital stay; t_4_ = day 14 of hospital stay; t_5_ = discharge from the ward; t_6_ = 30 days after discharge; t_7_ = 6 months after baseline

^b^With Outcome-oriented nursing assessment AcuteCare (epa-AC ©) the patient's abilities and impairments are assessed daily by registered nurses using the four-level epa point system and recorded in electronic form [50]

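### Mortality is due 30 days after discharge, but patient records are its only named source, so deaths outside the hospital may go uncounted

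*Protocol article*

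**What the plan says.** Table 1 (Overview of the evaluation of effects) lists five safety outcomes at patient level.

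- **Mortality:** "People with cognitive impairment that died during data collection". The source is patient records and the time point is t6.
- **Stability of care arrangements:** includes "Number of readmissions within 30 days". The source is "Telephone interview with people with cognitive impairment and/or their relatives", also at t6.
- **Falls:** "Number of falls documented", from patient records at t5.
- **Physical restraints:** "Occurrence of the use of physical restraints", rated by nurses at t2 to t5.
- **Antipsychotics:** "Newly prescribed antipsychotic medication during hospitalisation", from patient records at t5.

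The table footnote fixes the time points: "t_5_ = discharge from the ward; t_6_ = 30 days after discharge". The Data analysis section under Evaluation of effects says: "We will categorise and compare safety outcomes by frequency, relatedness, seriousness, and severity". It also promises close monitoring of mortality in both arms, with no difference expected. The Sample size section assumes a stay that is three days shorter under the intervention.

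**The concern.** The source named for mortality does not match its time point. Elsewhere in Table 1, patient records are the hospital's own documentation, such as daily nursing assessments, falls and type of admission. A death at home, in a care home or in another hospital would not reliably be entered there. The protocol handles other events after discharge differently, because the next row obtains them by telephone at the same t6.

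The gap need not be equal between arms. If the intervention shortens the stay, a death on a given day after admission is more likely to fall after discharge, where the named source sees less. For an intervention that aims at earlier discharge, death after discharge is a central safety question. Vital status that was never collected cannot be recovered by an analysis plan, so the source has to be settled at data collection.

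**Working it through.** **The plan's own figure.** The article gives no mortality rate and no mean stay, so no stated mortality figure can be reproduced. The only input used here is the 3-day reduction from the Sample size section. The power stated there does reproduce. The design effect is 1 + 119 × 0.05 = 6.95, the standard error is √((18² + 16²) × 6.95 / 360) = 3.35, and 3 / 3.35 = 0.90. With a critical value of 0 at a one-sided level of 50%, power is 81.5%. This has no bearing on the point.

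**Effect of the source (illustration, all rates assumed).** Let h be the share of control patients who die in hospital, d the share who die after discharge up to t6, and c the share of post-discharge deaths that the records capture. Assume equal true mortality in both arms. Assume also that the shorter stay moves one fifth of in-hospital deaths to after discharge (3 days out of an assumed 15).

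- Observed in control: h + c·d
- Observed in intervention: 0.8h + c·(d + 0.2h)

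| h | d | c | True, both arms | Observed control | Observed intervention | Observed ratio |
|---|---|---|---|---|---|---|
| 5% | 5% | 0.2 | 10% | 6.0% | 5.2% | 0.87 |
| 5% | 5% | 0.5 | 10% | 7.5% | 7.0% | 0.93 |
| 3% | 6% | 0.2 | 9% | 4.2% | 3.72% | 0.89 |
| 3% | 6% | 0.5 | 9% | 6.0% | 5.7% | 0.95 |

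The true ratio is 1.00 in every row. With complete capture (c = 1) both observed figures equal h + d and the distortion disappears.

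**Effect of the mortality window.** Follow-up runs from admission to 30 days after discharge. For an assumed control mean stay L, the ratio of window lengths is (L − 3 + 30) / (L + 30).

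- L = 12: 39/42 = 0.93
- L = 15: 42/45 = 0.93
- L = 20: 47/50 = 0.94

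The window shortens by 6% to 7%, which is small.

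**Effect on the in-hospital window.** For falls the window is the stay itself, so the ratio is (L − 3) / L: 0.75, 0.80 and 0.85 for L = 12, 15 and 20. Days at risk fall by 25%, 20% and 15%.

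**The case against.** The strongest reply is that Table 1 has an incomplete source column and that nobody plans to ignore known deaths. Dating mortality at t6 shows an intent to count deaths to day 30. Deaths in the index stay, or on readmission to the same hospital, are in the records. A call to patients or relatives would usually reveal other deaths, and participant flow is documented. This stands as far as it goes: it would be too strong to say that the records miss all deaths after discharge, and under-counting is an inference. But the table gives that call no role in mortality and asks for no date of death, so capture is left to chance.

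A reader might go further and infer that all safety comparisons shrink with the primary outcome and so hide harm. The article does not support that, for these reasons:

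- Readmissions have a fixed 30-day window, and the mortality window changes little.
- The sentence on comparing safety outcomes does not exclude rates. Fall counts and days in hospital are both collected, so a rate stays computable and may be set in an analysis plan that is not shown.
- Falls per stay is a legitimate measure of the patient's total burden. The article's own hypothesis is that fewer adverse events lead to shorter stays, so length of stay follows treatment and may itself depend on falls. Dividing by it brings its own distortion.
- A claim that a daily fall rate raised by 18% to 33% would be masked needs a constant daily hazard as well as an assumed mean stay. Nothing in the article supports the former.
- Restraints are recorded as occurrence at scheduled days, not as episodes, and mixed models over time are planned for secondary outcomes. New antipsychotic prescription appears to be a yes/no event per patient. Neither needs an offset for days in hospital.

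**Conclusion.** The concern holds for the mortality source. As written, deaths after discharge and outside this hospital can be missed, and possibly more often in the intervention arm if stays shorten. The size is unknown, because the article does not state what the records hold after discharge. The ratios of 0.87 to 0.95 rest on assumed death rates, assumed capture of 20% to 50% and an assumed shift of one fifth of in-hospital deaths. They show the direction and a plausible order of magnitude and are not estimates for this trial. If stays do not shorten, the under-count has no reason to differ between arms through this route, although absolute mortality would still be too low.

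The shorter in-hospital window is real arithmetic (15% to 25% under the stated assumptions). It justifies an optional supplementary display and does not make the planned safety comparison wrong.

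**What to change.** 1. In Table 1, name the t6 telephone contact as a source for mortality next to patient records, and record vital status and date of death in it. Report how many patients have unknown vital status at t6, by arm.
2. With the date of death, report mortality at a fixed horizon from admission, for example 30 days, next to mortality at 30 days after discharge. Since t6 always lies at least 30 days after admission, that horizon needs no longer follow-up.
3. Optionally, show falls per patient-day beside the per-stay counts, with both labelled. Leave restraints and new antipsychotics as planned.

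The cost is one item in a call that is already planned and a few added lines in the safety tables. No new visits or staff are needed. The first change has to be in place before the t6 calls are made; the other two can be settled at analysis.

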#### Blinding

Due to the nature of the intervention, blinding of participants, EPN providing the intervention, and researchers collecting data is not feasible. However, we will blind the biostatistician during data analyses regarding group allocation of clusters (neutral group IDs) and participating people with cognitive impairment.

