#### Data collection and management

We will use claims data from the hospital to determine the potential cost savings of the intervention. These will be available at the hospital controlling department. This data includes Diagnosis Related Groups (DRG) charges, length of hospital stay, cost weight, gender, and primary and secondary International Statistical Classification of Diseases and Related Health Problems (ICD) diagnoses. The data will be delivered pseudonymously to the evaluators via a secure data exchange platform. In addition, we will collect training costs consisting of salaries of the nursing staff, the costs of the lecturers as well as material costs for premises, catering and travel costs.

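### 30-day readmission, a safety outcome, is counted only by an unblinded telephone interview, although patient records are already consulted at the same time point

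*Protocol article*

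**What the plan says.** In Table 1 (section on outcomes, data collection and management), the patient-level outcome on stability of care arrangements has two items: "Number of readmissions within 30 days" and the perceived stability of the arrangement. Both are classed as secondary safety outcomes at t6, which the table footnote defines as "30 days after discharge". The source column has one entry for both: "Telephone interview with people with cognitive impairment and/or their relatives".

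Other entries in the same table use records. Length of stay, falls and new antipsychotic prescriptions come from patient records. So does mortality ("People with cognitive impairment that died during data collection"), which is also placed at t6. Where two sources are combined, the table shows it: unrecognised pain compares the research team's rating with the records, and sleep has both a self-rating and a record-based nursing assessment.

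The Blinding section states that "blinding of participants, EPN providing the intervention, and researchers collecting data is not feasible". The Discussion accepts that knowing the allocation could influence both participants' answers and data collection.

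The economic evaluation separately obtains administrative data: "We will use claims data from the hospital to determine the potential cost savings of the intervention". The fields listed there do not include later admissions.

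**The concern.** The trial's hypothesis is that person-centred care avoids adverse events, "leading to a reduction in the length of hospital stay". With length of stay as the primary outcome, a reader will want to know whether patients who leave sooner come back sooner. Of the listed safety outcomes, readmission answers that most directly.

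The chosen source is weak for this purpose in three ways.

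- **Recall.** Participants have cognitive impairment or are at risk of it. A relative may answer with or instead of the patient, which helps, but who answers then varies from case to case.
- **Non-response.** Someone not reached contributes no value, whereas the Data analysis section promises an intention-to-treat analysis without exclusions.
- **Unequal reporting.** According to the Intervention section, the expanded practice nurses coach relatives and hold case conferences on discharge planning. The intervention thus acts on people who may later report the outcome. Response or recall could differ between arms, in either direction.

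An analysis plan cannot repair this afterwards if the record data were never extracted.

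**Working it through.** **The plan's own figures.** No figure is given for readmission. The only power figure concerns length of stay, and it reproduces. The design effect is 1 + (120 − 1) × 0.05 = 6.95. The standard error is √[(18² + 16²)/360 × 6.95] = 3.35 days. The ratio 3/3.35 is about 0.90. At a one-sided 50% level the critical value is 0, so power is Φ(0.90) ≈ 81.5%, as stated in the Sample size section. The point here does not depend on it; only the 360 per arm and the design effect are used below.

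**Assumed inputs (none is in the document).** True 30-day readmission rate p = 18%, with 15% to 20% also shown. Share of all readmissions captured by interview s = 0.70 to 0.90. Share of readmissions that are to this hospital h = 0.60 to 0.90. Records are taken to show every readmission to this hospital.

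**1. Missed events by interview alone.** 0.18 × 360 = 65 readmissions per arm. With s = 0.75 to 0.85, the number missed is 65 × 0.25 to 65 × 0.15, that is 16 to 10 per arm.

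**2. Equal under-reporting.** The observed difference is s × (true difference). A true 15% versus 20% appears as 4.0 points at s = 0.8 and 3.0 points at s = 0.6. Two-sided 5% power with 360 per arm, ignoring clustering, is 42% with full capture, 34% at s = 0.8 and 26% at s = 0.6. With the design effect of 6.95 it is 10% or less in every case.

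**3. Unequal reporting.** With no true difference and p = 18%, capture of 75% versus 85% gives 0.18 × 0.75 = 13.5% against 0.18 × 0.85 = 15.3%, a spurious 1.8 points. With p = 20% and capture of 0.70 versus 0.90, the gap is 0.20 × 0.20 = 4 points. A true excess of 20% (intervention) over 15% (control) disappears if capture in the intervention arm is 0.15/0.20 = 0.75 of that in control.

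**4. What each source captures.** Interview only: s. Records only: h. Either source: h + (1 − h)s, if the interview finds admissions elsewhere with the same probability s.

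| h | s | Interview only | Records only | Either source |
|---|---|---|---|---|
| 0.60 | 0.70 | 0.70 | 0.60 | 0.88 |
| 0.60 | 0.90 | 0.90 | 0.60 | 0.96 |
| 0.80 | 0.80 | 0.80 | 0.80 | 0.96 |
| 0.90 | 0.70 | 0.70 | 0.90 | 0.97 |
| 0.90 | 0.90 | 0.90 | 0.90 | 0.99 |

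Records alone capture fewer events than the interview whenever h is below s. With h = 0.60 to 0.75 they miss 65 × 0.40 to 65 × 0.25, that is 26 to 16 per arm. The either-source count misses (1 − h)(1 − s) × 65. That is 0.40 × 0.25 × 65, about 6, at h = 0.60 and s = 0.75, and 0.25 × 0.15 × 65, about 2, at h = 0.75 and s = 0.85.

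**5. Effect on unequal reporting.** If h is the same in both arms, the spurious gap shrinks by the factor (1 − h). The 1.8 points in step 3 become 1.8 × 0.40 = 0.7 at h = 0.60 and 1.8 × 0.25 = 0.45 at h = 0.75.

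**The case against.** The strongest reply has four parts.

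**Records are not a better yardstick.** A reader might infer that the hospital's own records should be the main comparison because they exist for everyone. The documents do not support that. The study is in one hospital, and Table 1 does not restrict readmissions to it. Step 4 shows that records alone can capture less than the interview. The share returning to this hospital could also differ by arm, with three purposefully selected wards per arm and allocation following the ward managers' decision. This objection stands, and it is why records should supplement the interview.

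**The size is assumed, and small against the noise.** This also stands. At observed rates of 13.5% and 15.3%, the standard error of the difference is √[(0.135 × 0.865 + 0.153 × 0.847)/360] = 2.6 points. It is about 7 points if the length-of-stay design effect is borrowed (2.6 × √6.95). The illustrated 1.8 points is below one standard error either way. A bias is nevertheless worth removing when removal is cheap, because a larger sample would not reduce it.

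**The source may be less poor than it sounds.** A relative is likely to know of a hospital stay in the past month, deaths have their own record-based outcome, and the Discussion already admits the lack of blinding. This lessens the recall problem but leaves non-response and unequal reporting.

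**A journal article may leave cross-checks to the full protocol.** That carries little weight here, because Table 1 has a source column and names records wherever they are used, including where they accompany another assessment.

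**Conclusion.** The point holds as a moderate weakness in one safety outcome of an exploratory trial, and the change is worth making. What the document establishes is that readmission has a single, unblinded informant source, while patient records are consulted at the same time point for mortality. How many readmissions would be missed, and whether the arms would differ, is unknown. The 10 to 16 missed per arm and the 1.8-point gap rest wholly on the assumed 18% rate and 75% to 85% capture.

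Two stronger readings should be resisted. A reader might infer that the protocol designates readmission as its check on premature discharge. It does not; it labels the item a safety outcome under stability of care arrangements, and the link to early discharge is an inference from the primary outcome. A reader might also infer that the claims data could supply readmissions through one extra field. The economic evaluation describes a pseudonymous delivery with no readmission field, and no link to the trial's participant codes is described.

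The primary analysis, the sample size and the stated power are not affected.

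**What to change.** In Table 1, add patient records as a second source for the number of readmissions within 30 days. During the t6 record review already planned for mortality, count readmissions to this hospital within 30 days for every participant. Keep the telephone interview for admissions to other hospitals and for perceived stability.

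Compare the arms on the combined count, meaning a readmission found in either source. Report as supporting results the record-only count, stated to be complete for this hospital only, and the interview-only count, together with the interview response by arm.

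The cost is a small amount of extra record extraction and a few words in Table 1. The remaining limitation is that admissions to other hospitals still depend on the interview, so a participant who is not reached contributes only what this hospital's records show.
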